### ATTACH^TM^ pilot studies using innovative clinical trial and iKT approaches

The focus of ATTACH^TM^ on RF as well as the design of key intervention components were determined in collaboration with knowledge users including community health and social service agency administrators and health and social service providers. First, they pointed out that the most effective parenting programs tend to include a focus on RF [11, 75], and that these programs are few in number, thus RF became the target of ATTACH^TM^. Second, collaborators noted that existing RF-focused parenting programs typically involve months or years of psychotherapy provided by expensive clinical psychologists or psychiatrists [76], rendering these approaches cost-prohibitive and thus unrealistic in community settings. ATTACH^TM^ was thus designed to be a shorter intervention and simple enough to be administered by professionals with an undergraduate education in a health-related field, typical of partner agency staff. Third, many parenting programs tend to be designed for a narrow patient population (e.g., those affected by maternal addiction or depression, but not both) [77], making such programs difficult to administer in agencies serving more complex clients. Thus, ATTACH^TM^ was designed to help complex patients by targeting rapid learning of parental RF skills via practice, from which many could benefit. Finally, parenting programs often do not incorporate co-parents, defined as individuals who are a main source of parenting support (e.g., other parent, partners, grandparents, friends) [78, 79]. As a result, the inclusion of co-parents in ATTACH^TM^, was guided by health and social service providers /knowledge users’ suggestion [80].

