### Study setting {9}

#### Objective 1

Settings include our partner agencies in Alberta, Manitoba, and Saskatchewan that serve families experiencing toxic stress We will work with 100 new families from an initial 4 community agencies (Calgary Urban Project Society, Calgary, AB, Discovery House Women’s Shelter, Calgary, AB, Sonshine Community Centre, Calgary AB, and Steinbach Family Resource Centre, Steinbach, MB) and additional community partners (Elizabeth House, Calgary, AB, Regina Transition House, Regina, SK, Marymound, Winnipeg, MB, SOFIA House, Regina, SK, Elizabeth Fry Society, Ottawa, ON) are dissemination targets. The initial 4 implementation sites have a successful history of delivering programs focused on promoting health and development of children in families affected by toxic stress and provide an optimal testing ground for the ATTACH^TM^ intervention. Currently, these agencies do not offer any RF-based parenting programs. The ATTACH^TM^ program will be added on to their existing services or programs. and will disseminate knowledge to additional partners over the course of the study. **Objective #2:** For the qualitative component of the study, we will interview study participants who complete the ATTACH^TM^ intervention in the initial 4 community agencies (Calgary Urban Project Society, Calgary, AB, Discovery House Women’s Shelter, Calgary, AB, Sonshine Community Centre, Calgary AB, and Steinbach Family Resource Centre, Steinbach, MB), as well as their health and social service providers and agency administrators at the same partner agencies, using NPT [75, 76, 79] .

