##### Quantitative component

We will recruit until we have completed all study components with 100 new families, a sufficient *n* to detect minimum *d* = .34 for pre- /post- assessment differences in parent-child relationship quality. From discussions with agency health and social service providers and administrators, it will be feasible to recruit 30 families (including parents, co-parents, and children) from each agency, from patients currently seeking service, to retain 20 of them for 3 months postintervention for follow-up (any longer was deemed unrealistic given potential for patient relocation). Specifically, iKT and end-of-grant dissemination will be planned in partnership with agency health and social service providers and administrators.

#### Objective 2

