## Methods: data collection, management, and analysis

### Data collection methods {18a, 18b)

#### Objective 1: ATTACH^TM^ impacts

We have engaged with our agency partners on the collection of parents’ and children’s demographic information, descriptive data on exposure to toxic stressors, outcome measures, and covariates. To reduce participant burden, data on demographic variables will be obtained from agency administrative records as much as possible (e.g., ethnicity, sex, and gender, first language, marital status, education, employment, number of children, and age of patients and children) at pre-assessment. To further reduce burden, many measures have been selected from intake data collection already conducted in agencies, e.g. ASQ-3 [84]. Covariate measures will primarily be those already given at patient intake and that focus on toxic stress exposures, i.e. depressive symptoms [Edinburgh Depression Scale (EDS) [93, 94], a 10-item self-report tool to measure depression and exhibits sensitivity of 66.7–69% and specificity of 67.7% and takes 5 minutes to administer], family violence [Revised Conflict Tactics Scale-Short Form (CTS2-SF) [95], a 20-item questionnaire with internal consistency of 0.79–0.95 and takes 3 minutes to complete], addictions [Alcohol, Smoking and Substance Involvement Screening Test (ASSIST) [96], a measure of dependence on cannabis, cocaine, and other drugs over lifetime and past 3-months, with high levels of internal consistency, construct, concurrent and discriminant validity [97] and takes 15 minutes to complete]; and adverse childhood experiences [Adverse Childhood Experiences (ACE) [98] Questionnaire, consisting of 10 questions, with extensive reliability and validity data and takes less than 3 minutes to complete]. To get at patient strengths in the face of toxic stress, the Brief Resilience Scale (BRS) [99] will also be administered, a 6-item tool that with internal consistency ranging from .80–.91 and takes 3 minutes to complete. All questionnaire data will be collected at pre-assessments, post-assessments and at 3 months post-assessment follow-up by agency health and social service providers /ATTACH^TM^ interventionists, who will be trained and supervised to do so on REDCap (www.project-readcap.org) as part of the ATTACH^TM^ training program. Please see Additional file 3: Appendix 3 for Dried Blood Samples (DBS) Protocol for DBS collection.

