### Statistical methods {20a, 20b and 20c}

We will analyze the demographic characteristics of the sample with measures of central tendency and frequencies as appropriate. For all analyses, alpha will be set a priori at .05 (two-tailed).

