#### Objective 1: ATTACH^TM^ impacts

For (1a), Evaluate ATTACH^TM^ impacts on parent-child relationship quality (primary outcome), parental RF, and child development and (1d) evaluate long-term impact of ATTACH^TM^ (3 months delayed post-assessment), we will employ repeated measures analysis of variance (ANOVA), paired-t-tests, and chi-square tests to examine outcomes between pre-assessments, post-assessments and at 3 months post-assessment follow-up. For (1b) Determine whether ATTACH^TM^ is equally effective across patient populations (and for whom it works best/worst), we will examine differences among sub-groups derived from known covariates through use of independent samples *t*-tests (two groups, e.g., child sex), ANOVAs (more than 2 groups, e.g., race/ethnicity), repeated measures analysis of covariance (with identified covariate) and linear regression models (continuous covariate, e.g., age, years of education). For (1c) evaluate whether ATTACH^TM^ impacts immune biomarkers indicative of inflammatory disease risk, (i.e., gene expression, DNA methylation).

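### The tests named for objective 1b leave agency out, so a sub-group difference can reflect the delivering agency where a covariate is unevenly spread over agencies

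*Protocol article*

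**What the plan says.** In the protocol article, the Objective 1 paragraph under Statistical methods asks under 1b whether the programme is "equally effective across patient populations (and for whom it works best/worst". It names the methods:

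- For grouped covariates, "we will examine differences among sub-groups derived from known covariates through use of independent samples" t-tests (two groups, with child sex as the example) and ANOVAs (more than two groups, with race/ethnicity as the example).
- For adjustment or continuous covariates, "repeated measures analysis of covariance (with identified covariate) and linear regression models (continuous covariate, e.g., age, years of education".

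The error rate is common to all of these: "For all analyses, alpha will be set a priori at .05 (two-tailed".

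The covariates are listed under Data collection methods: "Covariate measures will primarily be those already given at patient intake and that focus on toxic stress exposures". They are the EDS (depressive symptoms), CTS2-SF (family violence), ASSIST (addictions) and ACE (childhood adversity). The BRS (resilience) and demographic items are collected as well. Agency and facilitator are in neither place.

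Other sections show that families are nested in agencies that differ. Study setting lists four initial sites: an urban project society, a women's shelter, and the "Sonshine Community Centre, Calgary AB, and Steinbach Family Resource Centre, Steinbach, MB". Recruitment gives five agencies. The Intervention and Recruitment sections say that each agency trains its own staff (at least 2, or 2–5). Study setting says that the programme is added to each agency's existing services. The account of the pilot studies says that narrowly targeted programmes are a poor fit, "making such programs difficult to administer in agencies serving more complex clients", so families with several stressors are expected.

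**The concern.** A two-sample t-test or a between-group ANOVA cannot adjust for anything. The covariance and regression models could, but the text describes each with one covariate. Two kinds of confounding of the sub-group contrast can follow.

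- **Agency.** If families in a sub-group are concentrated in one agency, the contrast also compares that agency's facilitators, background services and data collection with those elsewhere. Family violence is the plausible case, given a women's shelter among the sites.
- **Overlapping stressors.** If two stressors occur together and only one alters response, the other tested alone picks up part of its effect.

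At stake is the interpretation of 1b: weak delivery at one site could be read as a population that benefits less. This is separate from the precision of the overall pre/post change and from the number of tests.

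**Working it through.** **The plan's own figure first.** Sample size states "We will recruit until we have completed all study components with 100 new families" and a minimum detectable d of 0.34 pre/post. A paired t-test with n = 100, two-sided alpha 0.05 and d on the SD of the difference has noncentrality 0.34 × √100 = 3.4 and power 92.0%. The stated n is sufficient for the overall test, and this point does not affect it. The article gives no corresponding figure for a sub-group difference.

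**Inputs from the article.** 100 completing families; about 20 retained per agency (5 × 20 = 100; four agencies would mean 25 each); alpha 0.05 two-sided.

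**Assumptions, because the article gives no figures.** The agency intraclass correlation (ICC) of change, the share of each agency's families in the sub-group, and the outcome of the sub-group tests, taken as pre-to-post change with SD 1.

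**Step 1: agency effects with no true sub-group effect.** Simulation of 5 agencies × 20 families, 4,000 replicates, between-agency SD = √(ICC/(1 − ICC)), within-agency SD 1. The table gives the rate of false significance at nominal 5%, for the unadjusted t-test and with agency as a fixed factor.

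| Share in sub-group, by agency (%) | ICC | Unadjusted | Agency in model |
|---|---|---|---|
| Even: 50 in each | 0 to 0.10 | 5.0–5.2% | 4.8–5.3% |
| Moderate: 90/60/50/30/20 | 0.02 | 6.2% | 5.4% |
| | 0.05 | 7.4% | 4.6% |
| | 0.10 | 9.6% | 4.6% |
| Strong: 95/90/50/10/5 | 0.02 | 7.0% | 4.1% |
| | 0.05 | 11.9% | 4.4% |
| | 0.10 | 18.7% | 4.9% |

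**Step 2: one weaker agency.** Suppose one agency changes 0.34 SD less than the rest, and shares p1 of the sub-group and p0 of the comparison group attend it. The spurious gap is 0.34 × (p1 − p0). For 80% and 10% this is 0.34 × 0.7 = 0.24 SD.

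The sub-group size s is then fixed by the size A of that agency: 0.8s + 0.1(100 − s) = A, so s = (A − 10)/0.7.

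- A = 20: s ≈ 14. Noncentrality 0.238 × √(14 × 86/100) = 0.83; significant in 13% of trials.
- A = 25: s ≈ 21. Noncentrality 0.238 × √(21 × 79/100) = 0.97; significant in 16% of trials.

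At 60%/10% the gap is 0.34 × 0.5 = 0.17 SD, significant in 10–12% of trials. At the extreme 100%/0% it is 0.34 SD, significant in 27–31%.

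**Step 3: overlapping stressors.** If only stressor B alters change, by e SD, and the share with B differs by φ between families with and without A, then A tested alone shows φ × e. With e = 0.5 and 50 v 50:

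- φ = 0.3: 0.15 SD, significant in 11.5% of trials.
- φ = 0.4: 0.20 SD, 16.8%.
- φ = 0.5: 0.25 SD, 23.6%.

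**Context for precision.** The unadjusted sub-group difference detectable with 80% power is 0.57 SD at 50 v 50 and 0.71 SD at 20 v 80. A bias of 0.15–0.25 SD is therefore smaller than the real differences that 1b could reliably find.

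**The case against.** The article is condensed and an analysis plan may exist. Covariance analysis and regression can hold agency and several covariates; the parentheses may only match each test to a type of covariate, and nothing excludes agency. This stands in part: agency is unmentioned, not ruled out. But the article does name its tests, and the t-tests and ANOVAs cannot be adjusted, so a plan that follows this text would run them unadjusted.

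A reader might infer that agency differences will be reported as population differences, or that comparing violence-exposed with other families is largely comparing one agency with the rest. The documents do not support either. They give no stressor mix and no change by agency, and Study setting describes all four sites as serving families affected by toxic stress. The remark about complex clients suggests that stressors also mix within agencies. The article's own examples (child sex, race/ethnicity, age, education) are not the stressors, and an evenly spread covariate shows no inflation. Nor does any section tie 1b to a decision to withhold the programme from a population.

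It can also be said that a marginal description by population is a legitimate question in a study of naturalistic delivery, and that a model with all stressors and agency asks a different one and costs precision at n = 100. That is a fair reason to report the joint-stressor model beside the single-stressor results and not in their place. It is not a reason to omit agency, because 1b asks about populations and not sites.

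**Conclusion.** The point holds conditionally. The named 1b tests are unadjusted or take a single covariate, and agency is absent from both the analysis text and the covariate list. A sub-group difference can then reflect the agency and its facilitators, provided that the covariate is unevenly spread over agencies and that change differs by agency.

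Under the assumed ICCs of 0.02–0.10, the false-positive rate is about 6–10% with moderate and 7–19% with strong imbalance, against about 5% with agency in the model. A 0.34 SD agency shortfall with an 80%/10% split produces a 0.24 SD gap, significant in about 13–16% of trials when that agency holds 20–25 of the 100 families. The ICCs, the shares and the shortfall are assumptions, and reading the outcome as change is the natural interpretation, not stated text.

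The change is worth making because it is cheap, but it does not bear on the overall pre/post analysis.

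**What to change.** For 1b:

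1. Replace the unadjusted t-tests and ANOVAs with a model of pre-to-post change that includes agency as a fixed factor. In a repeated-measures form, use visit-by-covariate with agency-by-visit. Each contrast is then made within agencies.
2. Beside the single-stressor results, report a companion model holding the baseline EDS, CTS2-SF, ASSIST and ACE scores together.
3. Report any sub-group found almost wholly in one agency as not separable from that agency.
4. Label 1b findings as exploratory associations. Adjusting for agency does not supply a control group, and sub-groups may still differ through maturation or regression to the mean.

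The number of agencies (four in Study setting, five in Recruitment) should be reconciled when the agency factor is defined.

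The cost is analysis wording only: families are recruited through the agencies, so agency should be known for each, and four or five levels are feasible as a fixed factor with 100 families. The downside is somewhat wider intervals and no usable estimate for a covariate that hardly varies within agencies.

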#### Objective 2: ATTACH^TM^ implementation feasibility

Analysis will occur in two parts. First, interviews will be transcribed and coded and examined for key learnings that may offer guidance to implementation in agencies. These learnings will be shared with the Executive Team, PEC, and CEC and discussed so that appropriate adjustments may be made to facilitate ATTACH^TM^ normalization in agencies. Second, all transcripts will be coded using the stages of thematic analysis including familiarization, coding, theme development, and data reporting [100]. Theme and sub-theme development will be deductive, using a priori codes dictated by interview questions to explain factors that promote or inhibit interventions from being embedded in agency practice. Two trainees will code the data, supervised by [name], who is experienced in qualitative data analysis. Data will be managed with QSR International Nvivo12 [101]. Once themes and sub-themes are finalized, findings summarized in a draft report and shared with key informants as a validation check [101].

## Methods: monitoring

### Data monitoring {21a, 21b}

There is no data monitoring committee nor interim analysis since this is a social intervention, not the drug or pharmaceutical trial.

### Harms {22}

Any incidents (e.g., mental health crisis) observed by the investigators or facilitators will be recorded and managed as needed (e.g., with appropriate comfort measures and mental health referral). If the study staff interacting with these families observes any child abuse, they will report it to the Law Enforcement Authorities or act upon to intervene. The blood sample collection involves the potential for minor risk of discomfort, redness and swelling, and a rare risk of infection and fainting. However, these risks are small when blood samples are taken by trained staff, using standard blood sample collection procedures, and care will be taken to avoid these risks (see Additional file 3: Appendix 3). Moreover, due to the COVID-19 pandemic additional risks are associated with in-person participation.

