### Outcomes {12}

Parent-Child Relationship Quality will be measured with the Parent-Child Interaction Teaching Scale (PCITS) [81]. The PCITS is an observational binary measure of relationship quality in an everyday teaching situation, designed for children 36 months or younger. It is considered the gold standard for the assessment of parent-child relationship quality. The PCITS consists of 73 items categorized into six subscales including parental sensitivity to cues, responsiveness to distress, growth fostering, and cognitive growth fostering, child clarity of cues and responsiveness to parent as well as parent total, child total, and parent-child total scores. The scales’ reliability and validity are well established and was observed to be a strong measure of intervention impact in our pilot studies . The observation typically takes 5 minutes to administer and is videotaped to enhance the accuracy of data coding. ATTACH^TM^ interventionists who are health and social service providers in agencies, will be trained to administer the videotaping. Colleagues from the University of Washington will code all videos. During the pilot studies, they retained > 95% intra-rater reliability on 10% of recoded videos and reliable at the 90th percentile with the Canadian study team. Coders are supervised by PI [name] who has been a certified PCITS trainer since 1996 and has kept up annual certification. A protocol for data collection was developed as part of the pilot studies and discussions with patients revealed that the assessment is feasible and acceptable.

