## Ethics and dissemination

### Research ethics approval and consent or assent {24 and 26a}

Ethics approval has been obtained from the Conjoint Health Research Ethics Board (CHREB; Ethics ID: REB20–0903) of the University of Calgary, and all participants will undergo a process of informed consent. The University of Calgary is the lead agency conducting the study and partner agency research sites rely on CHREB’s approval as part of their agency ethics protocols. All funding and research guidance flows from the University of Calgary and partner agencies will not have access to the study data, nor will they be involved in data analysis or data storage. The participants will be asked to provide informed consent. We have created different consent forms for the individual interviews and intervention participation to clearly indicate to patients what they are consenting to participate in (see Additional file 1: Appendix 1 and Additional file 2: Appendix 2).

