### Confidentiality {27}

To protect confidentiality and anonymity of findings, all data will be held in confidence, numerically coded with identifying information removed, and stored on a secure network drive. No personal email addresses or accounts will be used for communication purposes or for data sharing. The staff will ensure that the participant signs the consent form to understand the privacy and confidentiality nature of the study in the beginning. Additional steps may include reiterating the privacy and confidentiality nature of the study before digital video-recording taping.

Parents’ demographic information including name and age will be collected by the partner agencies. With the exception of the consent form (stored separately), only de-identified data will be shared with the ATTACH^TM^ team. The demographic information will be used to describe our sample in future publications. Interactions between the parents and children will be digitally video recorded to assess parent child interaction quality. These assessments are age specific. Any video digital data will be password protected or encrypted. The researchers will not have access to identifying information as participants will only be identified with an ID number. Any identifying information will be removed from the beginning and replaced with an ID number for analysis. Only the research team will have access to questionnaire response data. All information provided by participants will be kept confidential, except when it needs to be reported as required by law (when participants express a desire to do harm to themselves or others). No participant will be identified in any publications or presentations that come from this research. The findings of this study will be reported as aggregate data at health conferences and in journal publications; however, any information that could identify the participants will not be included.

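### The harms rule joins reporting observed child abuse and intervening with *or*, so staff who intervene and record it but notify no outside authority have complied as written

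*Protocol article*

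**What the plan says.** Three statements in the protocol article bear on this point.

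- **Harms {22}, the abuse rule.** It reads: "study staff interacting with these families observes any child abuse, they will report it to the Law Enforcement Authorities or act upon to intervene". This is the only sentence in the article that tells staff what to do on seeing abuse.
- **Harms {22}, the general incident rule, two sentences earlier in effect and directly before it in the text.** "Any incidents (e.g., mental health crisis) observed by the investigators or facilitators will be recorded and managed as needed". The examples of management given there are comfort measures and mental health referral.
- **Confidentiality {27}.** Information that participants provide is kept confidential "except when it needs to be reported as required by law (when participants express a desire to do harm to themselves or others").

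On context, the Study setting section states: "Settings include our partner agencies in Alberta, Manitoba, and Saskatchewan that serve families experiencing toxic stress". One of the four initial sites is a women's shelter. The data collection section lists "family violence [Revised Conflict Tactics Scale-Short Form (CTS2-SF") among the toxic stress measures.

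**The concern.** A safety rule should not allow the weaker course to count as full compliance. Here the person who saw the abuse may choose between telling an authority and dealing with it personally, and the text treats the two as equivalent.

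The choice could arise in practice. The children are at most 36 months old and cannot speak for themselves. The families are recruited because they face toxic stress, and family violence is one of the exposures measured. Facilitators meet each parent for one hour a week over 10 weeks and film parent-child play, so they are well placed to see something. The article provides for no data monitoring committee and no auditing, so it names no independent body that would later notice an unreported event. Recruitment has begun, so the rule is already in use.

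What is at stake is child safety. Nothing in the effectiveness analysis depends on it.

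**Working it through.** The plan gives no figure here, so the check is a reading of the rule and of the text around it.

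**Step 1. What complies with the abuse rule.** Let R be a report to law enforcement and I an intervention. The rule is *R or I*.

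| Course taken | R | I | Complies as written |
|---|---|---|---|
| Report only | yes | no | yes |
| Intervene only | no | yes | yes |
| Both | yes | yes | yes |
| Neither | no | no | no |

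Three of the four courses comply, and one of those three contains no report to law enforcement. An exclusive reading of *or* would remove the third row but leave the second, so the result does not depend on how *or* is read.

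**Step 2. What intervening may include.** The article does not define it. The intervene-only row therefore covers two cases: (a) staff act by notifying a non-police body such as child protection, and (b) staff act themselves and notify nobody outside. In case (a) an outside authority has been told and there is no gap. Case (b) complies equally well, and it is the gap.

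**Step 3. Whether other text closes case (b).**

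- The incident rule requires the event to be recorded, so case (b) would leave an internal record. Recording and managing do not amount to notifying an authority.
- The confidentiality exception removes an obstacle to disclosure. It covers what participants provide, and its explanation is an expressed wish to harm oneself or others. It does not mention abuse that staff observe, and it does not instruct anyone to report.
- The sections on ethics approval, consent, training and recruitment say nothing on reporting abuse.

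Case (b) therefore stays open in the text shown.

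**Step 4. The same check on the reworded rule.** If a report to the competent authority is required and protective action is added where needed, two courses comply: report only, and report with protective action. Neither lacks a report. This holds only if the law at the site decides *who receives* the report. If the law also decided *whether* a report is made, a course without a report would comply wherever no law demanded one.

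**The case against.** The strongest reply has four parts.

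1. **The *or* may be protective in intent.** It may be meant to let staff contact a body other than the police. That is plausible, and it is why the gap is limited to case (b) above. It does not close that case, because the sentence does not say that intervening must include telling anyone.
2. **Abuse would not go undocumented, and the law applies whatever the article says.** Both statements stand. A reader might infer that the protocol lets abuse vanish without trace, or that it sets itself up as a substitute for legal duties. The documents support neither inference: incidents are to be recorded, and the confidentiality text acknowledges reporting that the law requires.
3. **A condensed article is not the operating procedure.** Facilitators are health and social service providers with 20 hours of training, and the agencies have ethics protocols of their own. The consent forms (Additional files 1 and 2) and the training material are not shown. It cannot be said from here that any staff member would act on the *or*, or even that they would consult this section. This limits the practical claim. It does not excuse the sentence, which states a rule and states it badly; nothing has been left to another document.
4. **No analysis changes.** That is correct, and it limits the weight of the point.

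A reader might also infer a gap for the staff who code the videos, since the rule names only staff who interact with families. The article does not support that as a finding, because the coders' procedures may be in documents not shown. No coder pathway is proposed.

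**Conclusion.** The point holds in a limited form. As written, a staff member who sees child abuse, intervenes and records it internally, but notifies no outside authority, has followed the Harms section. No text shown directs staff to report.

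The size cannot be quantified. The article gives no rate of observed abuse or of reporting, and the count of compliant courses only restates the logic. The effect is on child safety alone.

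The conclusion rests on the plain meaning of the sentence and on the text shown. It would weaken if the unseen consent forms or training material carry a clear instruction to report, though the article's sentence would then be at odds with them and should still be corrected. It is a correction the sponsor should make, at medium confidence, and is not a reason to doubt the study's results.

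**What to change.** Replace the sentence in Harms {22} with:

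> *If study staff observe any child abuse, they will report it to the competent authority (law enforcement or child protection, according to the law at the site) and, where needed, also act to protect the child.*

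This makes the report mandatory, turns intervention into an addition to it, and lets the recipient differ between provinces. The law at the site selects the recipient only and should not be worded as a condition on reporting.

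The cost is one minor wording amendment. "Ethics approval has been obtained from the Conjoint Health Research Ethics Board", so the change would go to that board. The article records no amendments so far, so this would be the first. The confidentiality text, outcomes, sample size and analyses stay as they are.
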